## Statistical methods

### Statistical methods for primary and secondary outcomes {20a}

#### Preliminary analyses and missing data

Frequency tables for all variables and measures of central tendency and variability for continuous variables will characterize the sample and be stratified by randomization group (i.e., intervention versus control). As recommended by CONSORT guidelines (http://www.consort-statement.org/), we will not do statistical tests comparing randomized groups at baseline. Our primary analyses will assume participants who drop out and have no available medical records have not achieved our outcome (e.g., HIV viral suppression) and therefore missing data will not affect the primary analyses. In additional analyses, we will relax this assumption and treat dropout as missing data. In addition, for our moderator (and mediator) hypotheses, there may be some missing data on self-reported syndemic factors, for example. The data analysis for this study will be generated using SAS software, Version 9.4, trademarks of SAS Institute Inc., Cary, NC, USA. The proposed analyses will be conducted using validated algorithms. All program code and results will be documented extensively and archived to enable future review, transparency, and result reproducibility.

#### Hypothesis 1

*THR* will be superior to off-site linkage to HIV care in achieving HIV RNA<200 copies/ml measured by the proportion of participants virally suppressed across the follow-up assessments.

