### Objectives {7}

The primary objective is to compare the efficacy of *THR* for initiation of ART at SSPs vs. off-site linkage to an HIV clinic with respect to viral suppression across follow-up (suppression at 3, 6, and 12 months post randomization). Participants with HIV RNA<200 copies/ml will be considered virally suppressed.

The primary hypothesis is that *THR* will be superior to off-site linkage in achieving HIV RNA<200 copies/ml measured by the proportion of participants virally suppressed across follow-up (time-averaged viral suppression).

The secondary objectives are to measure differences between study arms in MOUD initiation and HCV cure. Participants in the *THR* arm will have enhanced access to medical and mental health clinician visits via a telehealth platform and remote phlebotomy in addition to medication management (e.g., storage in pill lockers at SSP, weekly delivery) and appointment reminders. Participants assigned to the off-site linkage arm will be linked to a traditional Ryan White clinic by SSP staff as is currently the standard of care. MOUD initiation is measured by buprenorphine, naltrexone, or methadone on urine drug screen (UDS). HCV cure (i.e., HCV RNA undetectable) is defined as sustained virologic response after completing direct acting antivirals (DAA), i.e., SVR12. Mediating effects of the intervention on injection risk behaviors (i.e., syringe reuse and syringe sharing) will also be assessed.

For the economic analysis, *THR* is expected to have a higher cost but be more effective in increasing uptake of ART, MOUD, and DAA, as well as HIV viral suppression, MOUD retention, and HCV cure among PWID participants. Incremental cost-effectiveness ratios (ICERs) will be calculated to report the additional cost per unit of desired outcome (e.g., increased ART and MOUD initiation) in the *THR* vs. off-site linkage to HIV care arms.

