### Sample size {14}

Assuming *α* = 0.05, power=.80, and *N*=240, we computed the minimum detectable odds ratio (*OR*) and absolute proportion difference (*pdiff*), assuming the three post-intervention time points are part of the contrast. We varied the within-subject correlation *ρ* from 0.10 to 0.80. Power for a binomial is lowest when the base-rate (control group) probability (*P*_0_) is near 50%. Minimum detectable effects are 15% absolute difference in proportions and depend on the base-rate of suppression in the standard of care (*P*_0_) and the level of autocorrelation. This size of effect falls within published cutoffs of small to medium effect sizes [39].

Power analyses were generated using the generalized estimating equations-based two-group repeated proportion module in NCSS PASS 2020 to compute minimum detectable effect sizes for the proposed primary analysis. The study will begin with 240 participants evenly assigned to the intervention and control groups (80 per city). Our primary analysis strategy will assume any participant dropping out of the study has not achieved the outcome.

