## Assignment of interventions: allocation

### Sequence generation {16a}

Participants (*n*=240) will be randomized by block randomization to *THR* or off-site linkage to HIV care. All randomizations will be stratified by gender and site (Tampa vs. Miami vs. Ft. Lauderdale). Randomization will occur with central control using the REDCap program and will be external to the three sites to assure robust and unbiased approach. Participants are randomly assigned to one of two treatment groups in a 1:1 ratio. Randomization procedure will use a permuted-block randomization scheme to ensure relative balance across time. The block size is randomly permuted with varying block sizes [4, 6, 8] to prevent study staff from guessing group assignment. Randomization tables are separated by site and stratified by biological sex.

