#### Primary inferential analyses to address primary aim (Hypothesis 1)

We hypothesize that, for those randomized to the *THR* arm, the odds of our primary outcome, HIV viral suppression, will be higher than for those randomized to off-site linkage to HIV care (control) arm (Hypothesis 1). Generalized estimating equations (GEE) [54] will be used to perform the proposed primary analysis, which is a planned time-averaged comparison of post baseline measurements of HIV viral suppression across the *THR* and control groups to test primary Hypothesis 1. Alpha will be set at 0.05 for this planned comparison. Planned post hoc comparisons will examine the difference between conditions at each of the three assessment times.

Though GEE estimates are consistent even if the correlation structure is mis-specified, GEE’s statistical efficiency improves as the working correlation structure more closely approximates the actual correlation structure, so various correlation structures suitable for the study’s design will be considered (e.g., exchangeable, autocorrelated, *m*-dependent, unstructured). The QIC statistic will be used to select the final correlation structure. Recruitment city (Miami vs. Tampa or Ft. Lauderdale) will be included in all models as required by the stratified randomized design to obtain unbiased results. Robust standard errors will be used to obtain correct inferences even if the chosen correlation structure remains slightly mis-specified. All analyses will include outlier and influential case screening via computation of GEE-based residual analysis, including leverage, DFBeta, and Cook’s D statistics. If outliers are found, results will be reported with and without outliers included.

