### Methods in analysis to handle protocol non-adherence and any statistical methods to handle missing data {20c}

We will address any incomplete data with multiple imputation (MI) [57], which makes the relatively mild assumption that incomplete data arise from a conditionally random (MAR) mechanism [54]. Auxiliary variables will be included to help meet the MAR assumption.

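### Scoring dropouts as not suppressed does not stop missing data from affecting the primary analysis, and the article's three statements on missing outcomes need to be aligned

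*Protocol article*

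**What the plan says.** Three places in the protocol article deal with a missing primary outcome.

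- **Sample size {14}:** "Our primary analysis strategy will assume any participant dropping out of the study has not achieved the outcome". No exception is made for medical records.
- **Statistical methods {20a}, Preliminary analyses and missing data:** participants who drop out and have no available records "have not achieved our outcome (e.g., HIV viral suppression) and therefore missing data will not affect the primary analyses". Additional analyses will then drop the failure assumption and treat dropout as missing. The paragraph also foresees gaps in self-reported moderator and mediator data.
- **Methods to handle protocol non-adherence and missing data {20c}:** "We will address any incomplete data with multiple imputation (MI", under a missing-at-random assumption with auxiliary variables. It does not say which variables or analyses this covers.

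The secondary hypotheses take over the missing-data strategy of Hypothesis 1. The article gives no expected dropout rate, overall or by arm. Both failure rules speak of dropping out; neither mentions a single missed visit by someone still in the study.

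**The concern.** A failure score replaces an unknown value with a fixed one. It removes the gaps from the data set but not their influence on the estimate. If more results are missing in one arm, and some of those participants are suppressed, that arm's rate is pushed down further.

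The design gives a reason to consider unequal loss. Under Objectives {7} the THR arm receives "enhanced access to medical and mental health clinician visits via a telehealth platform and remote phlebotomy", together with weekly medication delivery and appointment reminders. Control participants are treated off-site by clinicians outside the study team, so rescuing a missed result from the records depends on outside charts. A control participant who is suppressed in outside care but whose result is not retrieved counts as a failure. Part of an observed advantage for THR could then reflect more complete measurement.

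A reader told that missing data cannot matter has no reason to look for this. Unaligned wording on the record exception and on multiple imputation also leaves room for dispute about which rule was primary.

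**Working it through.** **Inputs from the article.** "Alpha will be set at 0.05 for this planned comparison" (two-sided assumed). "power=.80, and *N*=240", and "Participants are randomly assigned to one of two treatment groups in a 1:1 ratio", hence 120 per arm. Three follow-up times. "We varied the within-subject correlation *ρ* from 0.10 to 0.80". Stated minimum detectable difference: 15 points. The introduction cites 44% suppression in an external cohort, used here as one control rate.

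**Assumed.** Exchangeable correlation, missing shares, and suppression among the missing.

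**Step 1: reproduce the plan's figure.** For a time-averaged difference, SE = √{[p₀(1−p₀) + p₁(1−p₁)] × (1+2ρ)/3 / 120}. At p₀ = 0.44, p₁ = 0.586, ρ = 0.5: SE = √(0.4890 × 0.6667/120) = 0.0521, and 0.146/0.0521 = 2.80 = 1.96 + 0.84. The detectable difference is therefore 14.6 points (14.5 at p₀ = 0.50). At ρ = 0.6 it is 15.1–15.3 points. Across ρ = 0.10–0.80 it runs from about 11 to 16–17. The stated 15 points is reproduced at mid-range correlation.

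**Step 2: bias with no true effect.** Let p be the true rate in both arms, m_T and m_C the missing shares, and s the suppressed share among the missing, taken as equal in both arms. The coded rates are p − m_T·s and p − m_C·s, so the spurious difference (THR minus control) is s × (m_C − m_T). Type I error is P(|Z| > 1.96) when Z has mean difference/SE.

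Example: p = 0.50, m_T = 0.10, m_C = 0.25, s = 0.5, ρ = 0.5. Coded rates are 0.45 and 0.375. SE = √[(0.2475 + 0.2344) × 0.6667/120] = 0.0517. The mean of Z is 0.075/0.0517 = 1.45, so type I error is 30.5%.

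| Missing THR / control | s | Spurious difference | Two-sided type I error (ρ = 0.5) |
|---|---|---|---|
| 20% / 20% | any | 0 | 5.0% |
| 15% / 20% | 30% | +1.5 points | 5.9% |
| 10% / 20% | 10% | +1.0 | 5.4% |
| 10% / 20% | 30% | +3.0 | 8.8% |
| 10% / 20% | 50% | +5.0 | 16.1% |
| 10% / 25% | 10% | +1.5 | 5.9% |
| 10% / 25% | 30% | +4.5 | 13.8% |
| 10% / 25% | 50% | +7.5 | 30.5% |
| 20% / 10% | 50% | −5.0 | 16.1% (against THR) |

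The 10% / 25%, s = 50% row runs from 46.5% at ρ = 0.10 to 24.6% at ρ = 0.80.

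**Step 3: equal loss with a real effect.** True rates 44% and 59%, 20% missing in each arm, and the missing as often suppressed as the rest of their arm. Coded rates: 0.44 × 0.8 = 35.2% and 0.59 × 0.8 = 47.2%, a difference of 12.0 points. At ρ = 0.5, power without loss is Φ(0.15/0.0521 − 1.96) = 82%; with loss it is Φ(0.12/0.0515 − 1.96) = 64%. At ρ = 0.3 the fall is from 90% to 74%, and at ρ = 0.8 from 71% to 53%.

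**The case against.** **Does the design favour THR?** A reader might infer that it does. The documents do not support that as fact. HIV RNA is a study laboratory measurement at 3, 6 and 12 months, paid equally in both arms. Every participant is a client of a syringe services program, and the retention section expects ongoing contact with all of them. Everyone signs a medical record release. Controls may be seen in clinics where study clinicians also work. Bias towards THR needs control participants to miss the study draw, be suppressed elsewhere and have no retrieved record, all more often than THR participants. This is possible but not shown, and it reverses if THR loses more. What remains is that these measures reduce loss without making it equal, and a signed release is not a retrieved result.

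**Is multiple imputation a second, conflicting primary rule?** Read literally, the word any in {20c} covers the primary outcome, and even visits after death. But {20a} announces additional analyses that treat dropout as missing and mentions gaps in moderators and mediators. Imputation can be read as serving those, and {20c} never calls it primary. Its scope is ambiguous; a flat contradiction is not established.

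**Are the scenarios severe?** The larger figures need both a wide gap in missingness and many suppressed participants among the missing. With 10% of the missing suppressed, type I error stays below 6%. That objection stands, so the whole range is shown.

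**Is the detail a matter for the analysis plan?** Record windows and sensitivity details often are. A false statement about what the primary rule achieves is not.

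**Conclusion.** The inference is wrong as written. Failure coding may be kept as the primary rule, but it is an assumption, neutral under the null only when missing share times suppression among the missing is the same in both arms. In the assumed scenarios with more loss under control, the spurious difference is 1 to 7.5 points, up to half of the 15-point detectable difference, and type I error at ρ = 0.5 ranges from about 5% to 31%. Equal 20% loss costs 3 of 15 points and about 18 percentage points of power at ρ = 0.5. The article gives no missing rates, so these figures show sensitivity and are not forecasts. The direction is open.

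Separately, {14} and {20a} differ on the medical-record exception, and {20c} does not say whether imputation reaches the primary outcome. Both are unresolved wording that can be settled cheaply before the data are seen.

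**What to change.** 1. In {20a}, delete the clause saying that missing data will not affect the primary analyses. Say instead that failure coding is an assumption whose effect depends on missingness by arm.
2. Put one primary rule in {14} and {20a}. It should cover missed visits as well as dropout, and use the same record sources and time windows in both arms.
3. In {20c}, limit multiple imputation to covariates, moderators, mediators and the additional analyses that treat dropout as missing.
4. Report missingness by arm and visit. Beside the primary result, show multiple imputation and an arm-specific delta (tipping-point) analysis, since imputation under missing at random alone does not test departures from that assumption.

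Do not make the superiority claim conditional on imputing only the control arm. If missing control visits took the control rate while missing THR visits stayed failures, a true 44% versus 59% with equal 20% loss would be compared as 44% versus 47.2%: 3.2 points, with power of about 9% at ρ = 0.5.

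Cost: wording changes, one extra sensitivity analysis and a more cautious statement of the primary result. Sample size and data collection are unchanged, apart from applying record retrieval equally in both arms.

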#### Primary inferential analyses to address primary aim (Hypothesis 1)

We hypothesize that, for those randomized to the *THR* arm, the odds of our primary outcome, HIV viral suppression, will be higher than for those randomized to off-site linkage to HIV care (control) arm (Hypothesis 1). Generalized estimating equations (GEE) [54] will be used to perform the proposed primary analysis, which is a planned time-averaged comparison of post baseline measurements of HIV viral suppression across the *THR* and control groups to test primary Hypothesis 1. Alpha will be set at 0.05 for this planned comparison. Planned post hoc comparisons will examine the difference between conditions at each of the three assessment times.

Though GEE estimates are consistent even if the correlation structure is mis-specified, GEE’s statistical efficiency improves as the working correlation structure more closely approximates the actual correlation structure, so various correlation structures suitable for the study’s design will be considered (e.g., exchangeable, autocorrelated, *m*-dependent, unstructured). The QIC statistic will be used to select the final correlation structure. Recruitment city (Miami vs. Tampa or Ft. Lauderdale) will be included in all models as required by the stratified randomized design to obtain unbiased results. Robust standard errors will be used to obtain correct inferences even if the chosen correlation structure remains slightly mis-specified. All analyses will include outlier and influential case screening via computation of GEE-based residual analysis, including leverage, DFBeta, and Cook’s D statistics. If outliers are found, results will be reported with and without outliers included.

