### Eligibility criteria {10}

Eligibility criteria include the following: (1) age 18 or older; (2) able to speak English; (3) enrolled in IDEA Miami, IDEA Tampa, or the SPOT SSPs; (4) injection drug use in past 12 months by self-report; (5) willing and able to sign informed consent, provide locator information and medical records release; (6) testing reactive for HIV by rapid test; and (7) HIV RNA>200 copies/ml as determined by on-site labs or abstracted medical records (result within 3 months of randomization date). Of note, pregnant people are eligible for enrollment in this trial.

Exclusion criteria include the following: (1) testing HIV negative via rapid test; (2) receipt of THR intervention in the past 6 months; (3) inability to provide informed consent; (4) planning to leave the area within 12 months; (5) principal or site investigator discretion; (6) currently in prison or jail; and (7) enrollment in NIDA Clinical Trials Network CTN 121. Investigator discretion could include serious medical, psychiatric, or co-occurring substance use disorder that acutely requires a higher or different level of care including the following: (1) disabling or terminal medical illness (e.g., decompensated heart failure, cirrhosis, or end-stage liver disease); (2) severe, untreated, or inadequately treated psychiatric condition (e.g., active psychosis); (3) in need of medical detox for severe alcohol, benzodiazepine, or other depressant or sedative hypnotic use; (4) suicidal intent or plan; or (5) homicidal ideation.

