## Data collection and management

### Plans for assessment and collection of outcomes {18a}

Data collection is planned at screening, baseline, and at 3-, 6- and 12-month follow-up assessments. Quantitative behavioral questionnaires will be available in English and completed in REDCap under multi-factor authentication at UM. Measures will be included from NIDA’s Data Harmonization projects, particularly NIDA’s Seek Test Treat and Retain for Vulnerable Populations data consortium. Table 1 describes the battery of quantitative assessments planned.

Laboratory assessments will include indicated laboratories in PWID. At screening, these will include HIV RNA to determine eligibility as well as T cell subsets, HCV RNA, HBsAg, HBsAb, anti-HAV, RPR, and 3-site gonorrhea and chlamydia screening. Additional laboratory assessments occur at 0, 3, 6, and 12 months. HIV RNA is measured to confirm primary outcome at 3, 6, and 12 months. HCV RNA and UDS are measured to confirm secondary outcome measures in both arms.

For the cost and cost-effectiveness analyses, we will perform an economic evaluation of *THR* versus off-site linkage to HIV care. We will look at the cost to achieve a unit of effectiveness as defined by the main study and, to the extent possible, will look at this from different perspectives (healthcare, societal). For cost data, we will create custom resource trackers based on the DATCAP method [40]. DATCAP was designed as a program-level costing instrument for standard modalities of SUD treatment.

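### The primary GEE names recruitment city as its only covariate; adding the pre-randomisation HIV RNA value that eligibility already requires would be a cheap, possibly modest gain in precision

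*Protocol article*

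**What the plan says.** The section on primary inferential analyses for Hypothesis 1 describes a GEE for a "planned time-averaged comparison of post baseline measurements of HIV viral suppression across the" randomised groups at months 3, 6 and 12. "Alpha will be set at 0.05 for this planned comparison". The section covers candidate working correlations, selection by QIC, robust standard errors and influence diagnostics. One covariate is named, recruitment city, which "will be included in all models as required by the stratified randomized design to obtain unbiased results". Baseline HIV RNA is not placed in any model in the article.

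A pre-randomisation value nevertheless exists for everyone. Eligibility criteria {10} require "HIV RNA>200 copies/ml as determined by on-site labs or abstracted medical records", with the result no more than 3 months from randomisation. Section {18a} lists the assay among the screening tests: "At screening, these will include HIV RNA to determine eligibility as well as T cell subsets" and other tests. It then names HIV RNA at months 3, 6 and 12; laboratory work is also planned at month 0, but HIV RNA is not named there.

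Sample size {14} fixes N at 240, alpha at 0.05 and power at 0.80, and solves for the detectable effect: "Minimum detectable effects are 15% absolute difference in proportions and depend on the base-rate of suppression in the standard of care" and on the within-subject correlation, which was varied "from 0.10 to 0.80".

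**The concern.** The primary outcome is HIV RNA dichotomised at 200 copies/ml. Its binary form is constant at entry, because everyone must be above 200, so it cannot serve as a covariate. The underlying quantity is not constant. Eligibility sets no upper limit, and pre-screening admits both people with a new reactive test and people with known HIV who are out of care or non-adherent. Continuous log10 HIV RNA could therefore carry prognostic information that the named model does not use.

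What is at stake is power at a sample size that is hard to enlarge. The article anticipates recruitment difficulty, has added a third site because of it, and under Interim analyses {21b} allows for a smaller target with a conditional-power threshold of 0.5. A covariate already in hand is one way to gain information without more participants. It also takes account of chance imbalance in baseline viral load, which otherwise remains as part of the random error that the standard error already covers.

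**Working it through.** **Inputs from the article.** N = 240, so 120 per arm ("The study will begin with 240 participants evenly assigned to the intervention and control groups (80 per city"); alpha 0.05, taken as two-sided because sidedness is not stated; power 0.80; three follow-up visits; detectable difference 15 points; within-subject correlation ρ from 0.10 to 0.80; control rate P0 not fixed, with values near 50% named as the worst case.

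**Input not in the article.** R², the share of variance in a participant's time-averaged suppression that baseline log10 HIV RNA explains. It is assumed here, over the range 0.01 to 0.20.

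**Step 1: reproduce the 15 points.** For 50% versus 65%, the two-proportion formula needs 170 per arm with a single measurement. Averaging three exchangeable visits multiplies this by (1 + 2ρ)/3. At ρ = 0.55 the factor is 0.70, giving 170 × 0.70 = 119 per arm, or N = 238. The stated figure therefore reproduces for ρ of about 0.53 to 0.57 (N = 234 to 244).

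It does not describe the whole stated range. With N = 240 and P0 = 0.50, power for 15 points is 96.2% at ρ = 0.1, 82.4% at ρ = 0.5 and 71.6% at ρ = 0.8.

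**Step 2: effect of adjustment.** Adjustment multiplies the residual variance by (1 − R²). From an 80% start:

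power = Φ[(1.960 + 0.842)/√(1 − R²) − 1.960]

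For example, at R² = 0.10: 2.802/√0.90 = 2.953; 2.953 − 1.960 = 0.993; Φ(0.993) = 0.840.

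N for unchanged power is 240 × (1 − R²), rounded up to an even number. The detectable difference is 15 × √(1 − R²).

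| R² (assumed) | Power | N for the same 80% | Detectable difference (points) |
|---|---|---|---|
| 0 | 80.0% | 240 | 15.0 |
| 0.01 | 80.4% | 238 | 14.9 |
| 0.02 | 80.8% | 236 | 14.9 |
| 0.05 | 82.0% | 228 | 14.6 |
| 0.10 | 84.0% | 216 | 14.2 |
| 0.20 | 87.9% | 192 | 13.4 |

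At the unfavourable end of the article's range (ρ = 0.8, P0 = 0.50), the same calculation moves power from 71.6% to 73.8% at R² = 0.05, 76.1% at 0.10 and 80.9% at 0.20.

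**Step 3: simulation of the logistic GEE with robust standard errors.** Without and with the covariate, 600 runs per scenario gave:
- no prognostic value: 86.0% and 85.5%
- R² about 0.02: 86.0% and 85.7%
- R² about 0.05: 87.2% and 88.5%
- R² about 0.11: 83.7% and 88.2%

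The Monte Carlo standard error of each figure is about √(0.86 × 0.14/600) = 1.4 points.

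A separate simulation with 4,000 runs per cell, 44% versus 59% and a visit correlation of 0.49 gave 81.4% and 81.2% with no prognostic value. With a baseline-outcome correlation of 0.33 (R² = 0.33² = 0.11) it gave 81.5% and 85.7%. Both simulations build the prognostic strength in. They check the formula and do not show that R² is large.

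**The case against.** The strongest reply is that nothing here is wrong. A randomised comparison by city-adjusted GEE with robust standard errors is valid without baseline viral load, and chance imbalance is already reflected in its standard error. Covariate lists are often settled in an analysis plan, and section {17a} refers to a finalised plan to be confirmed before data lock. A reader might infer that the trial will adjust for city and nothing else. The article does not say so: it says that city will be included and names no other covariate. All of this stands, and it limits the point to a suggested improvement.

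The gain may also be small. Entry is truncated at 200 copies/ml, and pre-screening selects people unlikely to be suppressed, so the range may be restricted. Dropouts without records count as failures, so the outcome partly measures retention, and nothing in the article links retention to viral load. This stands too: with R² of 0.05 or less the gain is about 2 points at most.

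Three stronger readings are tempting but unsupported:
- That the trial was sized at exactly 80% power for 15 points. N was fixed and the effect solved for, and power for 15 points ranges from about 72% to 96% across the stated ρ at P0 = 0.50.
- That baseline HIV RNA is measured uniformly on everyone. A value exists for everyone, but it may be an abstracted record up to 3 months old.
- That this is the only precision available without more participants. T cell subsets are also collected at screening and might serve.

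The reply does not remove the point that the model is described in detail, with one named covariate, while a plausible prognostic value is already in hand for every participant.

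**Conclusion.** The point holds as an inexpensive improvement, not as an error. The named primary model leaves out a baseline value that eligibility guarantees, and so may forgo some precision at N = 240. From an 80% start, the gain is about 0.4 points of power at R² = 0.01, 2 at 0.05, 4 at 0.10 and 8 at 0.20, with essentially no loss at R² = 0. These sizes rest on an assumed R² that the article does not give, a two-sided alpha, and the approximation that adjustment scales the residual variance by (1 − R²).

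A reader might infer that the planned estimate is biased, or that a substantial loss of power has been shown. The article supports neither.

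**What to change.** Before data lock, pre-specify in the primary GEE, beside the site term, the latest HIV RNA value on or before randomisation, as continuous log10 copies/ml. Use the same covariate in the planned comparisons at each visit. Report the standardised (g-computation) time-averaged difference in proportions with robust standard errors next to the odds ratio; this matches the absolute difference used in the sample-size section. Keep the city-only model as a sensitivity analysis.

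The cost is a short addition to the analysis plan, one standardisation step and one extra model, with no new data collection. There are two downsides. The adjusted odds ratio is conditional, so it targets a different quantity from the city-only odds ratio, which is why the standardised difference is needed. The age and source of the baseline values vary, which may shrink the gain but does not bias the randomised comparison.

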The alpha will be set at .05 for each these secondary hypotheses (2a, 2b, 3a, and 3b). In each model, recruitment site (Miami vs. Tampa or Ft. Lauderdale) will be included in these analyses as required by the stratified randomized design to obtain unbiased results. To maximize rigor, appropriate diagnostics including outlier and influential case screening will be examined for each model. If outliers are found, results will be reported with and without outliers included.

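### Randomisation is stratified by three sites and by sex/gender, but the main-effect models carry only site, in wording that can be read as two levels; the tests become slightly conservative

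*Protocol article*

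**What the plan says.** Protocol article, Sequence generation {16a}: "All randomizations will be stratified by gender and site (Tampa vs. Miami vs. Ft. Lauderdale"). The same paragraph ends: "Randomization tables are separated by site and stratified by biological sex". Allocation is 1:1 in permuted blocks of 4, 6 and 8. That makes six site-by-sex strata, with two names for the second factor.

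Protocol article, primary inferential analyses (Hypothesis 1): "Recruitment city (Miami vs. Tampa or Ft. Lauderdale) will be included in all models as required by the stratified randomized design". The secondary hypotheses (2a, 2b, 3a, 3b) follow the same rule: "recruitment site (Miami vs. Tampa or Ft. Lauderdale) will be included in these analyses as required by the stratified randomized design to obtain unbiased results".

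Sex appears in the two subsections on sex as a biological variable. There a sex-by-treatment interaction is added in a separate analysis of each hypothesis. No section lists sex or gender as a covariate in a main-effect model.

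**The concern.** The article states a rule (the stratified design dictates what goes into the model) and then meets half of it. This is not a detail left to an unseen analysis plan, because both the covariate and the reason for it are given.

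The site term adds a second difficulty. The randomisation section lists three sites side by side. The analysis sections set Miami against Tampa or Ft. Lauderdale. Read literally, that is a two-level contrast pooling a site housed in an academic medical center with one based at a Federally Qualified Health Center (Study setting {9}).

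Stratified blocks force near-balance on site and sex, so the treatment estimate varies less from trial to trial than under simple randomisation. A model that leaves out a prognostic stratifier does not credit that reduction, and its standard error is too large for the design used. The plan's robust standard errors do not repair this: they protect against a wrong working correlation. At stake is some power in a trial of 240 that already expects recruitment difficulty.

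**Working it through.** **The plan's own figure.** Sample size {14} gives a minimum detectable difference of 15 points at 80% power, alpha 0.05, N = 240, three visits and ρ from 0.10 to 0.80. Take 120 per arm and set d = (1.96 + 0.84) × √{[P₀(1−P₀) + P₁(1−P₁)] × (1+2ρ)/3 / 120}. For P₀ of 0.40 to 0.50, d is about 11.3 to 11.4 points at ρ = 0.10, 14.5 to 14.6 at ρ = 0.50 and 16.4 to 16.6 at ρ = 0.80. The stated 15 lies inside this range. The article does not say which P₀ and ρ produced it, and the point below does not depend on it.

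**Inputs from the article.** N = 240, 80 per city; one third women; three follow-up visits; alpha 0.05, taken as two-sided.

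**Assumed, because the article gives no value.** ρ = 0.5; outcome variance 0.25 at each visit; suppression gaps by sex of 5, 10 or 15 points; a gap between Tampa and Ft. Lauderdale of 20 points.

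**Approximate calculation (linear scale).**

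1. Variance of a participant's mean outcome: 0.25 × (1 + 2 × 0.5)/3 = 0.1667.
2. Variance due to sex: gap² × (1/3)(2/3).
3. Variance due to Tampa/Ft. Lauderdale, lost only if they are pooled: two thirds of participants lie 10 points either side of the pooled mean, so (2/3) × 0.10² = 0.0067.
4. Share R² = omitted variance / 0.1667. Standard error overstated by the factor 1/√(1−R²). Actual type I error 2 × [1 − Φ(1.96/√(1−R²))]. Power Φ(2.80 − 1.96/√(1−R²)), set to 80% when the standard error is right.

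| Omitted | Variance | R² | SE factor | Type I error | Power |
|---|---|---|---|---|---|
| Sex, 5-point gap | 0.0006 | 0.3% | 1.002 | 4.96% | 79.9% |
| Sex, 10-point gap | 0.0022 | 1.3% | 1.007 | 4.85% | 79.6% |
| Sex, 15-point gap | 0.0050 | 3.0% | 1.015 | 4.7% | 79.2% |
| Sex 15 points, and sites pooled with 20-point gap | 0.0117 | 7.0% | 1.037 | 4.2% | 77.9% |

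In participants, the last row is 240 × [1 − ((1.96 + 0.77)/2.80)²], about 12. The 15-point row gives about 5.

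**Simulation of the planned kind of model.** The simulated trials had 240 participants, six strata, blocks of 4/6/8, three binary visits and a participant random intercept with SD 2 (assumed). They were analysed by logistic GEE with independence working correlation and robust standard errors, with 4,000 trials per setting. Sex and site effects are assumed subject-specific odds ratios (ORs), site effects relative to Miami. Monte Carlo error is about 0.003 for type I error.

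| Setting | Model | Type I error | Power |
|---|---|---|---|
| No sex or site effect | all models | 0.051 | 0.867 to 0.869 |
| Sex OR 3, no site effect | three-level site | 0.049 | 0.843 |
| | three-level site + sex | 0.053 | 0.857 |
| Sex OR 2; sites OR 2 and 0.5 | two-level site | 0.045 | 0.831 |
| | three-level site | 0.052 | 0.842 |
| | three-level site + sex | 0.053 | 0.847 |
| Sex OR 3; sites OR 3 and 1/3 | two-level site | 0.034 | 0.793 |
| | three-level site | 0.047 | 0.827 |
| | three-level site + sex | 0.053 | 0.837 |

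In the last setting under no treatment effect, two-level site gives a mean robust standard error of 0.205 against a true SD of 0.190, 8% too large. With three-level site and sex the two are 0.208 and 0.210, so the standard error matches the design.

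**The case against.** The strongest reply is that the part which is certain is small. Only the omission of sex is beyond doubt. The site phrase may be a three-level factor with Miami as reference, or a sentence loosely adapted when the third site was added. With site at three levels, leaving out sex costs 0 to about 1.5 power points in the simulations, and nothing if sex is not prognostic. The error is conservative, and the finalised analysis plan is to be confirmed before data lock. All of this stands, and it sets the size of the point. It does not remove the gap between the stated rule and the models.

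A reader might infer more than the article supports:

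- *That the sites are definitely collapsed to two.* The wording allows that reading but does not settle it, and 4 of the 7 variance points in the worst row depend on it.
- *That 0.07 × 240, about 17 participants, is lost.* That measures excess variance. Balance is already delivered by the blocks, so the power loss corresponds to about 12.
- *That the reported intervals would narrow.* In a logistic model, adding covariates moves the log odds ratio and its standard error together. In the strongest simulated setting the mean standard error went from 0.205 to 0.208. The gain is in power.
- *That all secondary tests lose as much.* For a single binary outcome (2a, 3a, 3b) the same gaps give R² = 0.0117/0.25 = 4.7%. Hypotheses 3a and 3b use only participants HCV-positive at baseline, a subset on which randomisation was not stratified, so the mismatch there is weaker.
- *That some participants have no defined stratum.* Two terms are used for one factor, while allocation is encoded centrally in REDCap. This needs a wording clarification.
- *That leaving out baseline HIV RNA is an error.* Nothing in the article promises that adjustment. It is an option.

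**Conclusion.** The point holds in a limited form. The main-effect models omit one of the two stratifiers that the plan's own rule calls for, and the other is worded ambiguously. The tests are conservative as a result. The comparison is not biased by the omission, so the article's stated reason for including site, unbiased results, is not the right one either; the reason is a standard error that matches the design.

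The likely cost runs from negligible (sex only, small gap) to about 2 power points on the linear approximation (sex and pooled sites, gaps of 15 and 20 points). The most extreme simulated setting loses 4.4 points (0.837 to 0.793). All of these rest on assumed sex and site effects. The correction is worth making because it needs nothing that the trial does not already hold.

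**What to change.** In the primary model and in the models for 2a, 2b, 3a and 3b, state that site enters as a three-level factor (Miami, Tampa, Ft. Lauderdale) and that the sex/gender variable used in the REDCap randomisation table enters as a covariate. Say which variable that is and use one term for it throughout. Replace the unbiasedness rationale with agreement between analysis and stratified allocation.

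The odds ratio is then conditional on site and sex, so name that target and report a standardised risk difference beside it. Adjustment for baseline log10 HIV RNA may be considered separately.

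The cost is a few sentences in the analysis plan before data lock, with no new data. The one trade-off is the conditional odds ratio, which the standardised risk difference covers.
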